### Eligibility criteria {10}

#### ***Inclusion criteria*** [49]

Age 40–70 years old [50]Meet the diagnostic criteria for shoulder coagulation, with significantly limited shoulder range of motion (less than 100° in forward flexion, less than 10° in external rotation, and less than L5 level in internal rotation) [12] and an MRI diagnosis of rotator cuff injury (conducted by professional radiologists from the Imaging Department).Voluntarily participate in this experiment and sign the informed consent

#### Exclusion criteria [49]

Patients who are allergic to anesthetic drugs or have skin damage, ulceration, or infection at the anesthesia puncture site, and have long-term fever symptomsPatients with severe osteoporosisCoexists with other serious heart, liver, kidney, and other important organic diseases and blood diseasesPatients with obvious upper limb, neck, and shoulder blood vessel or nerve injury or fracturePregnant or lactating womenThose who are currently participating in other clinical trialsThose who suffer from mental and psychological diseases and cannot cooperate

#### Shedding criteria

After inclusion, the treatment was not completed according to the planned protocol;Serious adverse events occur during the treatment and, hence, cannot continue;The patient’s symptoms worsened, and it was not suitable to continue participating in the trial.

#### Eligibility criteria for physicians performing the interventions:

The physicians must have participated in Good Clinical Practice (GCP) training.They should hold a valid Chinese National Vocational Physician Certificate in Orthopedics.The physicians must be licensed to practice medicine legally in China.The physicians must have the qualification to conduct MUA in their respective hospitals.

### Interventions {11a}

#### Intervention description

Eligible patients will be randomized in equal proportions between the trial group (manipulation under anesthesia) and the control group (intra-articular steroid injection), undergoing a corresponding operation on day 1 and a sequent physical exercise for 14 days.

##### Trial group

The MUA will be performed by several physicians from the three hospital settings. These physicians are highly experienced and senior practitioners, with extensive backgrounds in conducting MUA for many years within their own hospitals. Additionally, prior to commencing the trial, all participating physicians underwent rigorous training with three standard operating procedure (SOP) sessions to ensure uniformity and consistency in the procedure. The MUA will be performedin the operation room to ensure safety and sterility. Before the operation, the patient needs to fast for at least 6 h. During the operation, the patient will continuously inhale oxygen at a low flow rate (2–2.5 L/min), open the intravenous infusion channel, and monitor the patient's vital signs in real-time with ECG monitoring.

A professional anesthetist of corresponding hospitals applies the brachial plexus block anesthesia in the operation room. The specific procedures are as follows: the patient lies down in a supine position, the head turns to the unaffected side, and a soft pillow is placed under the neck and shoulder to fully expose the anesthesia puncture site. After routine disinfection, the intermuscular groove formed by the sternocleidomastoid muscle and the anterior and middle scalene muscles, located under ultrasound guidance, is the entry point, where 10 ml (or 75 mg) ropivacaine + 10 ml 2% lidocaine is injected to block the brachial plexus. After 15–20 min of anesthesia, manual release begins.

##### Trail group: manipulation under anesthesia

①The patient takes a supine position. While the operator stands on the affected side of the patient, lifts the affected limb to 180° in flexion, holds the elbow of the affected side with one hand during the operation, and places the other hand on the upper end of the humerus near the humeral head at the patient’s axilla to prevent shoulder dislocation. Repeat three times when the sound of the adhesion loosening can be heard and the feeling can be felt.②Abduct and lift the patient’s affected limb to 180°, while also being mindful of protecting the humeral head to prevent dislocation. Repeat three times.③Flex the affected side shoulder joint to 90° in forward flexion, bend the elbow, and internally rotate the affected side shoulder joint to 45°. Repeat three times when the sound of the adhesion loosening can be heard and the feeling can be felt.④Rotate the affected shoulder in the neutral position, the 45° abducted position, the 90° abducted position, the 135° abducted position, and the straight-elbow position of the glenohumeral joint. Repeat three times.⑤The patient lies on the healthy side, with the shoulder joint extended, internally rotated, and the elbow flexed so that the patient’s fingers can touch the healthy scapula. Repeat three times. After the operation, immobilize and protect the affected limb.⑥After the operation, in the ward and with the patient under continued anesthesia, release the affected limb every hour for two times to achieve complete release of the shoulder joint.

*Note:* During the operation, pay attention to enhancing communication with the patient and closely monitoring the patient’s vital signs. The technique should be gentle to avoid the possibility of complications such as fractures due to improper operation.

##### Control group: intra-articular steroid injection

The intra-articular steroid injection procedure are as follows: Thoroughly sterilize the affected shoulder, inject 2 ml of chitosan and 2.5 ml of Diprospan diluent into the posterolateral approach of the shoulder joint cavity, and inject 2.5 ml Diprospan into the supraspinatus tendon, subacromial bursa, and long head of biceps tendon, respectively.

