# A multi-center, single-blinded, randomized, parallel-group, superiority study to compare the efficacy of manipulation under anesthesia versus intra-articular steroid injection in the treatment of patients with frozen shoulder and a diagnosis of rotator cuff injury or tear by MRI: study protocol for a randomized controlled trial

**DOI:** 10.1186/s13063-023-07810-2

**Published:** 2023-11-27

**Keywords:** Adhesive capsulitis, Frozen shoulder, Rotator cuff injuries, Manipulation under anesthesia, Intra-articular steroid injection

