## Abstract

**Background:**

Frozen shoulder (FS) is a common condition that can cause severe pain and limited range of motion in the shoulder joint. While intra-articular steroid injection has been shown to be an effective treatment for FS, manipulation under anesthesia (MUA) is an alternative treatment that has gained popularity in recent years. However, there is a lack of evidence regarding the effectiveness of MUA on FS patients with concomitant rotator cuff injury or tear. Though a few studies have shown that MUA is not associated with rotator cuff tears, and will not exacerbate the injury, more high-quality studies with bigger sample sizes are needed. Therefore, the aim of this multi-center, single-blinded, randomized, parallel-group, superiority study is to compare the efficacy of MUA versus intra-articular steroid injection in the treatment of FS patients with a diagnosis of rotator cuff injury or tear by MRI.

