### Explanation for the choice of comparators {6b}

Intra-articular steroid injection is a common treatment of FS [37], providing short-term benefits [37, 46, 47], and also proving effective for rotator cuff tear [48]. It is an effective, common, affordable treatment with little direct transformation to the shoulder structure, that is why we choose it as our control group’s treatment.

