## Objectives {7}

The objective of this trial is to observe the safety and efficacy of MUA, compared to intra-articular steroid injection, in the treatment of FS patients diagnosed with rotator cuff injury or tear by MRI. We hypothesize that the course of the disease can be shortened by MUA with quicker functional recovery and gain in the range of motion and a subsequent faster return to work compared to steroid injection treatment. Also, preoperative and sequent MRI and musculoskeletal ultrasounds will be applied to patients before and 6 months post the intervention to evaluate the condition of the patient’s rotator cuff injury or tear.

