## Trial design {8}

This trial is a randomized, controlled, prospective, multicenter superiority trial with two parallel groups. Patients with FS accompanying MRI diagnoses as rotator cuff injury or tear are randomly divided into two groups: the trial group (with manipulation under brachial plexus block anesthesia as the main intervention) and the control group (with intra-articular steroid injection as the main intervention). All patients included in this study will undergo a program of shoulder exercises, normally commencing within 24 h after the corresponding intervention, with three sessions per day lasting for 2 weeks. The data will be collected before the intervention, 1 day, 2 weeks, 4 weeks, 12 weeks, and 24 weeks after the intervention. Randomization will be performed by a computer-generated random number table with a 1:1 allocation.

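### The comparator is named as intra-articular steroid injection, but the procedure described adds chitosan and steroid at three sites outside the joint, so between-arm claims hold only for that combined regimen

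*Protocol article*

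**What the plan says.** All references are to the protocol article.

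**The name.** The title sets "manipulation under anesthesia versus intra-articular steroid injection in the treatment of patients with frozen shoulder". The abstract's aim is to "compare the efficacy of MUA versus intra-articular steroid injection". Objectives {7} assesses MUA "compared to intra-articular steroid injection", and Trial design {8} describes the control group as one "with intra-articular steroid injection as the main intervention". Statistical methods, Outcomes {20a}, expresses complications as rate ratios of MUA to intra-articular injection. The Discussion expects MUA to do better than the intra-articular steroid injection group and says that confirmation could change the standard of care.

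**The procedure.** The section on the control group opens with "The intra-articular steroid injection procedure are as follows". It then lists two steps:

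- in the joint: "inject 2 ml of chitosan and 2.5 ml of Diprospan diluent into the posterolateral approach of the shoulder joint cavity";
- at further sites: "inject 2.5 ml Diprospan into the supraspinatus tendon, subacromial bursa, and long head of biceps tendon, respectively".

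The trial group's description includes neither chitosan nor steroid. Both groups do the same 14 days of exercise.

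**The concern.** The name describes one drug class at one site. The procedure has two agents and four sites. Chitosan is not a steroid, and the bursa and the two tendons are listed apart from the joint cavity. The article presents every component as the intra-articular procedure itself and marks none as an adjunct.

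What is at stake is the meaning of the result. A clinician who injects steroid into the joint only would read the title and conclusion as saying what MUA did against that practice. The trial does not test that. The same applies to safety: Outcomes {20a} counts tendon injury among the complications, and the reference group for the rate ratio is one in which two tendons are injected, a fact that the label hides.

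This is not a detail left to a fuller document. The article states the regimen and also states a name that does not describe it.

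**Working it through.** No figure in the plan has to be reproduced here. The check sets the name against the procedure and then counts sites and volumes.

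**Step 1: name against procedure.**

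| Element | Comparator as named | Control procedure as described |
|---|---|---|
| Agents | steroid | Diprospan and chitosan |
| Joint cavity | yes | yes |
| Subacromial bursa | no | yes |
| Supraspinatus tendon | no | yes |
| Long head of biceps tendon | no | yes |

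The name is also used in Explanation for the choice of comparators {6b}, Interventions {11a}, the timeline table and Data collection {18a}, and in the shorter form without the word steroid in Blinding mechanism {17a}. None of these places mentions chitosan or a second site.

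**Step 2: sites.** 1 in the joint + 3 outside = 4. The share outside is 3/4. Two of the three outside sites are tendons, and one of those (supraspinatus) belongs to the cuff.

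**Step 3: volumes.** Inputs from the control-group section: 2 ml chitosan and 2.5 ml Diprospan diluent in the joint, and 2.5 ml Diprospan for the three other sites. The wording leaves open whether that last 2.5 ml is per site or in total, so both readings are shown.

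| | 2.5 ml at each site | 2.5 ml shared over the three sites |
|---|---|---|
| Outside the joint | 3 × 2.5 = 7.5 ml | 2.5 ml |
| All Diprospan or Diprospan diluent | 2.5 + 7.5 = 10.0 ml | 2.5 + 2.5 = 5.0 ml |
| Share of it outside | 7.5/10.0 = 75% | 2.5/5.0 = 50% |
| Total injected | 2 + 10.0 = 12.0 ml | 2 + 5.0 = 7.0 ml |
| Share of total outside | 7.5/12.0 = 62.5% | 2.5/7.0 = 36% |

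These are shares of volume, not of steroid dose, because the dilution is not given.

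**Step 4: what randomisation identifies.** Patients are randomised to MUA plus exercise or to the full injection package plus exercise. The between-arm difference estimates the effect of the one package against the other. No arm receives joint-only steroid, so nothing in the design separates the contribution of the joint injection from that of chitosan or the other three sites.

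**The case against.** The best defence is that the regimen is disclosed. Agents, volumes and sites stand under the control-group heading, and a short arm name after one full definition is ordinary practice. Trial design {8} speaks of the main intervention, which leaves room for adjuncts. Ancillary and post-trial care {30} calls the treatments routine at these hospitals. No sentence says outright that the effect belongs to intra-articular steroid alone.

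Part of this stands: an attentive reader can find out what was given, and the harm lies in interpretation. It does not rescue the name. The control-group section calls no component an adjunct, routine use does not make a label accurate, and the title, objective, contrast and conclusion are the places that carry the claim to readers.

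Three stronger readings are tempting, and the documents do not support them:

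- *The control arm is biased for or against MUA.* The extra agent and sites could make the control stronger or weaker than a joint-only injection. The article does not say which.
- *The planning rate for the control group comes from a different regimen.* Sample size {14} calls its source both a shoulder cavity injection and intra-articular steroid injection, the trial's own label. Without the cited study, no mismatch can be shown.
- *The rationale for the comparator fails.* It says the treatment was chosen as one "with little direct transformation to the shoulder structure, that is why we choose it as our control group", which sits awkwardly with injecting a cuff tendon. But the same section also cites benefit in rotator cuff tear, and an article may leave a justification of each component to the full protocol.

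**Conclusion.** The point holds as one of naming and interpretation. The comparison is internally valid, but only for MUA against the combined injection regimen. Efficacy results and the complication rate ratio cannot be attributed to a contrast with intra-articular steroid alone.

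The part that the name leaves out is not small: three of four sites, chitosan, and half to three quarters of the Diprospan or Diprospan diluent by volume. The range covers both readings of the 2.5 ml. It rests on the article's own separation of the joint cavity from the other three sites, and it says nothing about dose.

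The before-and-after assessment of the cuff in the MUA group (Safety evaluation; Additional analyses {20b}) is not affected, because it does not depend on the comparator.

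**What to change.** Settle which text is right.

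- **If the described procedure is what patients receive:** name the comparator in the title, the objective, the complication contrast in Outcomes {20a} and the conclusions as a combined intra-articular and peri-articular/tendon steroid plus chitosan injection. Limit every between-arm claim to that regimen.
- **If joint-only steroid is intended:** correct the control-group procedure. It is the only description of that procedure in the article for the three hospitals.

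The first route changes wording in the protocol and the final report only. Allocation, endpoints and sample size stay as they are. The cost is a narrower claim: the trial could no longer be presented as a test of MUA against intra-articular steroid as such.

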##### Post-procedural physiotherapy (PPP)

Patients from both groups will initiate a 14-day functional exercise, starting on the first day after the intervention treatment. A uniformly and strictly trained physician guides the first functional exercise of the patients until the patients and their accompanying family members have mastered the correct exercise method. They can record relevant videos, and family members can assist and supervise patients in the initial exercise stage. Physicians follow up with patients regularly to ensure the standardization and correctness of exercise posture.

The specific methods are as follows:①Forward elevation: The patient stands facing a wall with their feet shoulder-width apart and toes touching the wall. The fingers of the affected arm are spread out and placed on the wall. Slowly elevate the arm along the wall until the limit of pain tolerance is reached. The unaffected arm can assist in lifting the affected arm, or another person can push the scapula of the affected side from behind to help raise the arm to the maximum position.②Forward flexion with shoulder support: The affected shoulder is flexed to 90° with the elbow flexed. The palm of the unaffected hand is gradually placed on the elbow, moving it towards the midline to bring the affected arm to rest on the opposite shoulder joint.③Extension with internal rotation: The patient sits or stands with the palm of the affected hand facing backward and extends the shoulder joint. Within the limit of pain tolerance, gradually rotate and adduct the affected arm while bending the elbow until the fingers touch the opposite scapula. The unaffected hand can assist the affected hand in completing the exercise.

Repeat the above movements after the patient’s pain is relieved. Perform three sets of each exercise, three times per day.

The ROM, CMS, MPQ, VAS, and PPI numbers or scores will be collected at 1 day, 2 weeks, 4 weeks, 12 weeks, and 24 weeks after the intervention. Additionally, imaging examinations will be conducted during the 24-week visit. Due to the nature of the physical examinations required, all follow-up time points must be completed by the patients at the hospital’s outpatient or inpatient departments.

### Modifications{11b}

The study allows participants to exit voluntarily, or they may be removed by study clinicians if they experience negative effects related to the study or meet the shedding criteria during the treatment. If a participant leaves due to negative effects, the study clinicians will assess if they need further treatment. Safety data will be collected for all participants who leave the study. Patients from both groups may receive additional treatment after their exit. Patients who experience severe pain and cannot tolerate MUA therapy or show no improvement within a short period of time, impacting their quality of life and sleep, should receive emergency medication such as the use of painkillers, muscle relaxants, or other medications which are deemed absolutely necessary for the participant’s well-being and then be removed from the trial.

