### Concomitant care {11d}

The care of a patient awaiting surgery may involve administering pain relief medication to alleviate discomfort, providing guidance on how to properly take care of the affected arm (e.g., weight bearing on the upper limbs), and offering general advice on preventing additional stiffness in the limb. This will not include a specific home exercise program, as it is considered as an active intervention. After the surgery, the use of painkillers, muscle relaxants, and other medications is prohibited during the trial period. However, if there are specific circumstances such as intolerable pain, emergencies or unforeseen medical conditions, and any other situation, deemed necessary by the treating physician to ensure the patient's health, where these drugs are absolutely necessary, they must be accurately recorded on the medication registration form. Patients who had pre-existing medical conditions before enrollment will continue with their initial treatment, and any medication administered for pain relief will be noted in the medication record form. If a patient drops out of the trial or has poor compliance, the detailed reasons for this will be recorded in the case observation form, and efforts will be made to contact the patient frequently to obtain their understanding and support. Any efficacy-related measures that can be completed will be recorded, and the final treatment time will be noted. The patient’s compliance and adverse reactions will be described statistically and compared between the two groups.

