### Outcomes {12}

#### Primary outcome measures

##### Comprehensive efficacy evaluation (total effective rate)

Assessment was made primarily with reference to measurements of external range of motion of the glenohumeral joint and improvement in pain.

The specific judgment is as follows:①Cured: Shoulder pain disappears, forward flexion>150°, abduction>120°, extension>45°, and internal and external rotation>60°.②Effective: Shoulder joint pain basically disappears, with forward flexion from 120° to 150°, extension from 30° to 45°, abduction from 90° to 120°, and external and internal rotation from 45° to 60°.③Improved: Shoulder pain is reduced, and the range of motion is increased compared with that before treatment, but there is still limitation of movement.④Ineffective: no change in indications and symptoms before and after treatment.

The total effectiveness rate = (cure + effective + improved) / number of patients × 100%

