### Participant timeline {13}

Patients with FS will be randomly divided into the trial group and the control group. All patients included in this study will receive their disseminated treatment on Day 1 and undergo a program of shoulder exercises, for 2 weeks. The relevant data will be collected before the intervention, 1 day, 2 weeks, 4 weeks, 12 weeks, and 24 weeks after the intervention, while safety evaluations and adverse events will be recorded each visit. The specific participant’s timeline is shown in Table 1.

**Table 1 Tab1:** Participant’s timeline

Timepoint (state unit)	−7~0 DAY	Treatment day	1 day	2 weeks	4 weeks	12 weeks	24 weeks
Visit number:	1	2	3	4	5	6	7
Enrollment:							
Eligibility screen	x						
Informed consent	x						
Allocation	x						
Imagining examination	x						x
Baseline questionnaire	x						
Interventions:							
Intra-articular steroid injection		x					
Manipulation under anesthesia		x					
2-week shoulder exercises			x	x			
Assessments:							
Active range of motion		x	x	x	x	x	x
Passive range of motion		x	x	x	x	x	x
CMS		x	x	x	x	x	x
MPQ		x	x	x	x	x	x
VAS		x	x	x	x	x	x
PPI		x	x	x	x	x	x
Total effectiveness rate							x
Safety evaluation		x					x
Adverse event		x					x

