## Statistical methods

### Outcomes {20a}

The data will undergo encoded analysis and various patient details, such as their baseline information, range of motion, CMS, VAS, MPQ, PPI, duration of symptoms before treatment, and past histories, will be compared and summarized between the groups. The outcome variables of all patients will also be summarized by treatment group and time, following descriptive statistics such as the number of patients, mean and standard deviation (or median and interquartile range) for continues variables, and relative frequencies for categorical variables. The number of participants included in each analysis will be reported, and we will adhere to the intention to treat principle regarding the group assignment.

Differences between the various treatments will be calculated using one-way ANOVA statistics; the follow-up data of each group will be statistically analyzed using ANOVA of repeated measures if they conformed to normal distribution and chi-square, and if they do not, the rank sum test will be used; logistic regression will be used to analyze the correlation between each treatment method and the efficacy. The study will categorize complications by types, such as infection, post-operative pain, nerve, blood vessel, tendon, or bone injury, and count them overall. Poisson regression analysis will be used with corrections for overdispersion when appropriate. The impact of treatment on complication rates will be expressed as MUA to intra-articular injection rate ratios. The safety of the treatment will be evaluated by identifying and summarizing any adverse events that occur during the study. All treatment effects will be reported with their 95% confidence intervals and *p*-values. The statistical analysis will be conducted using the IBM SPSS statistical package (version 25.0).

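### Patients who need rescue medication for lack of early improvement are to be removed from the trial, which ties loss of the week-24 primary outcome to poor response and undercuts intention to treat

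*Protocol article*

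**What the plan says.** All references are to the protocol article.

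- **Modifications {11b}.** Patients with severe pain who cannot tolerate MUA, or who "show no improvement within a short period of time, impacting their quality of life and sleep, should receive emergency medication", get that medication for their "well-being and then be removed from the trial". The length of the short period is not given. For leavers, this section says "Safety data will be collected for all participants who leave the study" and allows further treatment after exit. It mentions no efficacy data.
- **Shedding criteria.** A patient may also be taken out when "symptoms worsened, and it was not suitable to continue participating in the trial", after a serious adverse event, or when treatment was not completed as planned.
- **Concomitant care {11d}.** Painkillers and similar drugs are prohibited after the procedure, but when they are unavoidable "they must be accurately recorded on the medication registration form". Removal is not mentioned. For dropouts, efficacy measures that are still feasible are to be recorded. Analysis population and missing data {20c} says much the same.
- **Primary outcome measures.** The only failure category of the total effective rate is Ineffective, defined as "no change in indications and symptoms before and after treatment". In Table 1 (Participant timeline {13}) the row "Total effectiveness rate" is marked at 24 weeks only.
- **Statistical methods, Outcomes {20a}.** The analysis commitment is "we will adhere to the intention to treat principle regarding the group assignment".

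**The concern.** The removal is from the trial, not just from study treatment. Treatment is one procedure on day 1 followed by 14 days of exercise, so after two weeks removal takes away little except follow-up.

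The trigger is poor response, close to what the primary outcome counts as failure. The decision lies with study clinicians who know the allocation (Blinding mechanism {17a}), and the period they must judge is undefined. If removed patients have no week-24 result and fail more often than the rest of their arm, that arm's effective rate is biased upward. Analysis by assigned group cannot recover outcomes that were never collected.

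The effect on the difference between arms depends on who is removed. MUA is the only treatment named for intolerance, and removal mainly from MUA would inflate its advantage. If the same share of failures leaves both arms, the advantage shrinks, because control is planned to have many more failures (57.2% v 13.8%).

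Concomitant care {11d} and Modifications {11b} also treat a rescued patient differently. One asks for a record and the other for removal, so sites may act differently.

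**Working it through.** **Inputs from the protocol (Sample size {14}).** Planned effective rates are 0.862 for MUA and 0.428 for injection, with 160 randomised per group and two-sided alpha 0.05. The planned difference is 0.862 − 0.428 = 0.434. Planned failures are 160 × 0.138 ≈ 22 on MUA and 160 × 0.572 ≈ 92 on injection. The 160 per group does not follow from the stated inputs (the usual two-sided formula gives 18 per group, or 20 with 10% dropout). That is a separate matter; 160 serves here only as the arm size.

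**Assumptions.** The documents give no removal fraction, so a range is shown. Patients without a week-24 result are assumed to leave both numerator and denominator.

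**1. Only failures are lost.** If a share *f* of an arm's week-24 failures is unobserved, the observed rate is p / (p + (1 − p)(1 − f)).

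- MUA, f = 0.25: 0.862 / (0.862 + 0.138 × 0.75) = 0.862 / 0.9655 = 0.893
- Injection, f = 0.25: 0.428 / (0.428 + 0.572 × 0.75) = 0.428 / 0.857 = 0.499

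| Share of failures lost | MUA rate | Injection rate | Difference, MUA-only loss | Difference, both arms | Difference, control-only loss |
|---|---|---|---|---|---|
| 0 | 86.2% | 42.8% | 43.4 | 43.4 | 43.4 |
| 10% | 87.4% | 45.4% | 44.6 | 42.0 | 40.8 |
| 25% | 89.3% | 49.9% | 46.5 | 39.3 | 36.3 |
| 50% | 92.6% | 59.9% | 49.8 | 32.6 | 26.3 |

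Differences are in percentage points.

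**2. Removed patients are a mixture.** Not every early non-responder would fail at week 24. If a share *r* of the arm is removed and a fraction *q* of those are failures, the observed rate is (p − r(1 − q)) / (1 − r). For MUA with r = 0.05:

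- q = 0.138 (the arm average): (0.862 − 0.0431) / 0.95 = 0.862, no bias
- q = 0.5: (0.862 − 0.025) / 0.95 = 0.881
- q = 1: 0.862 / 0.95 = 0.907

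**3. No true difference.** With both true rates set at 0.80 (an assumption), 160 per arm, a pooled z-test and 100,000 simulated trials, loss of failures from MUA only gives these two-sided rejection rates: 5.0% with no loss, 6.5% with 10% lost, 16.0% with 25% lost.

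**4. Removed patients kept in the denominator as ineffective.** The rate becomes p − r(1 − q). For MUA with r = 0.05 this is 0.862 at q = 1 and 0.837 at q = 0.5. The upward bias disappears, at the price of scoring some eventual responders as failures.

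**The case against.** The strongest objection concerns the denominator. The protocol defines the total effective rate over the number of patients and commits to intention to treat, so a removed patient without a favourable rating could be read as staying in the denominator and counting as not effective. Steps 1 to 3 then would not apply. That reading is possible, but no section states it. The figures are therefore conditional.

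Follow-up after exit is partly covered, because two sections ask that feasible evaluations still be completed and the safety sentence does not say safety data alone. This makes loss of the week-24 result likely rather than certain. Neither section requires a week-24 visit for a removed patient, and every assessment needs attendance at the hospital.

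The trigger is also narrower than lack of improvement: it requires an effect on life and sleep and medication judged unavoidable. Early non-response need not mean failure at week 24 in a condition that often resolves, and Improved is a low bar. This stands, and the mixture case with zero bias reflects it.

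At the planned rates the conclusion would survive. With half of control failures lost, 0.862 on 160 against 0.599 on about 114 gives a standard error of √(0.862 × 0.138/160 + 0.599 × 0.401/114) ≈ 0.053 and z ≈ 4.9. That stands too, but it holds only if the large planned effect is real; step 3 shows the exposure when it is not.

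Finally, handling of missing outcomes can be left to an analysis plan. That is fair for the counting rule. It does not reach the removal instruction, because an analysis plan cannot restore follow-up that the protocol tells clinicians to end.

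**Conclusion.** The concern holds. The protocol instructs a response-related removal after randomisation, decided by unblinded clinicians against an undefined time limit. This undercuts its own intention-to-treat commitment and fits poorly with its record-only rule for rescue drugs.

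The direction of bias is unresolved. For 10% to 50% of failures lost, the planned 43.4-point difference would be observed as 44.6 to 49.8 points (MUA-only loss), 42.0 to 32.6 (both arms) or 40.8 to 26.3 (control-only loss). With equal true rates of 80%, MUA-only loss of 10% or 25% of failures raises the false-positive rate from 5% to about 6.5% or 16%. These figures rest on assumed removal fractions, on loss confined to failures, and on removed patients leaving the denominator. There is no bias if those removed fail at their arm's average rate.

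This should be fixed because the instruction is explicit, it touches the primary outcome and the remedy is cheap. Confidence is medium because the size is unknown.

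**What to change.** 1. In Modifications {11b}, replace removal from the trial with stopping study treatment or giving recorded rescue. Keep all randomised patients in the scheduled visits to week 24 unless they withdraw consent, and apply the same to the shedding criteria.
2. Use one rule for both arms, give the short period a length, and align the section with Concomitant care {11d} so that a rescued patient clearly stays in.
3. Analyse all randomised patients by assigned arm, using observed week-24 outcomes where they exist. Count those who left for worsening or lack of improvement and have no week-24 outcome as Ineffective.
4. Add a sensitivity analysis that counts all rescued or removed patients as ineffective. Defining rescue as medication for the study shoulder avoids catching drugs for unrelated conditions.

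**Cost.** An amendment, which under Protocol amendments {25} needs the funding commission's agreement and ethics approval; an analysis rule; and some additional attendances at visits already in the schedule. No extra patients or new assessments are needed. Recruitment began in January 2023, so patients already removed would have to be invited back where their week-24 date allows. The reported effective rate may be lower.
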